#### 4.2.3 Exploratory Outcome Measures

The moderating effect of experiences in migration, integration and demographic variables on the efficacy of the intervention will be explored. To measure these exploratory outcomes the instrument IPL will be used. This is a 24-item instrument that measures the psychological, economic, social, navigational, linguistic and political integration in migrant groups. Another exploratory objective is to identify characteristics associated with success of the implementation. Therefore, a survey on demographics will be administered. This survey will include questions on age, gender, place of residence, marital status, employment situation, employer, current occupation, highest educational level achieved, year and month of arrival to Perú.

The IPL and the demographics form will be administered via a secure link to REDCap before the first session of the intervention.

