| Design/Methodology:             | 
Migrants will be randomized to receive the intervention (<math>n = 60</math>) or wait list control (<math>n = 30</math>). Mental health outcomes (PHQ9, GAD7, PCL5) will be assessed at baseline during screening, throughout the intervention, post treatment, and at 1-, 3-, and 6- months follow-up. Demographic information, the IPL will be assessed at the time of enrollment. LEC5 will be assessed at baseline and at 1-, 3- and 6-month follow-up. Acceptability will be assessed after each session. All assessments will be conducted by the research team through a secure link in REDCap. Each migrant will participate in 5 assessment sessions and 6-12 intervention sessions with prior assessment of mental health outcomes. The intervention sessions have a frequency of once a week. In the case of the waitlist control, mental health outcomes will be assessed at baseline at the time of enrollment and at endline 12 weeks after baseline. Once the endline has been assessed, they will receive the intervention, with corresponding assessments as described previously. In the case of the providers, feasibility and acceptability will be assessed after each session. See Appendix for a graph of the design, schedule and assessments.
 |

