There will be a planned variation in the dosage of the intervention, which can comprise 6 to 12 sessions. The exact number of sessions will be implemented according to the presentation of symptoms and difficulties of the participant. For instance, if the participant presents depressive symptoms concurrent with PTSD, then, strategies for the treatment of depression will be included alongside with strategies for the treatment of PTSD and the number of sessions will be higher. Also, some components identified as important for this population, such as problem solving or emotional regulation, could be added to the intervention, if they are identified as relevant for the specific participant. For instance, if - alongside with the CMD symptoms - the participant presents concrete problems that need to be tackled (e.g. precarious housing conditions, or lack of and need of childcare support), then the “problem-solving” component will be included as part of the intervention and the number of sessions will be higher. As described in detail in Section 8 “Study Intervention”, the first 6 sessions will be intended to treat the most urgent symptoms, and the following sessions will tackle other aspects relevant to the mental health of the participants.

As to the collection of data for the assessment of study objectives, the participant outcomes will be measured using validated instruments such as the PHQ9, GAD7, LEC5 and PCL5. In the case of the intervention group, all outcomes will be measured in the screening, after the last session and at 1-, 3- and 6-month follow-up. In the case of waitlist control, primary outcomes will be assessed at baseline during screening and at endline 12 weeks after baseline. For both the waitlist control and the intervention group, The PHQ9, GAD7, and PCL5 will be assessed throughout the intervention (which occurs at randomization for the intervention group, and 12 weeks after for the waitlist control group).

Furthermore, the assessment of secondary outcomes, such as acceptability and feasibility, will be measured as presented above, in section 4.

See the Appendix for a schematic of the study design.

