| Screening/baseline                                       | Begin: January 2025 and as potential participants contact research team until n =                                                                                    | Remotely via REDCap secure link (PHQ9, GAD7, PCL5, LEC5, demographics, exclusion criteria).                                                                                                                                                                                                                                                                                                                                                                                                                                                                                                                |
| Participation consent and enrollment                     | Begin: January 2025 and as potential participants contact research team until n = 90 is reached                                                                      | A link to the consent form will be sent via WhatsApp. A call will be scheduled to present the information on the study, clarify doubts and verify comprehension. Electronic consent will be collected via REDCap or DocuSign.                                                                                                                                                                                                                                                                                                                                                                              |
| Randomization and communication on begin of intervention |                                                                                                                                                                      | Remotely via telephone call
Demographics form via REDCap secure link
IPL via REDCap secure link                                                                                                                                                                                                                                                                                                                                                                                                                                                                                                      |

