|-------------------------------------|--------------------------------------------------------------------------------------------------------------------------------------------------------------------------------------------|-------------------------------------------------------------------------------------------------------------------------------------------------------------------------------------------------------------------|
|                                     | May-August 2025

Third group of 30 participants:
August -November 2025                                                                                                            |                                                                                                                                                                                                                   |
| Sessions 7 to 12                    | First group of 30 participants:
May - August 2025

Second group of 30 participants:
August-November 2025

Third group of 30 participants:
November 2025-February 2026 | Individually with provider
Remotely via Meet or WhatsApp videocall
60 min duration
Focus on other aspects relevant to mental health (emotional regulation, problem solving, adaptation related distress) |
| Assessments throughout intervention | January 2025 to February 2026                                                                                                                                                              | Remotely via REDCap secure link (PCL5 every week before the session, PHQ9 and GAD7 every 2 weeks before the session, acceptability and adherence every week after each session)                                   |
| Endline                             | May 2025 to February 2026                                                                                                                                                                  | Remotely via REDCap secure link (PHQ9, GAD7, LEC5 and PCL5)
12 weeks after first session in intervention group (or within 14 days of completion).
12 weeks after baseline in waitlist control group.        |

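### The IPL and the demographics form are timed inconsistently, and nothing secures their completion before allocation in both arms

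*Protocol*

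**What the plan says.** The protocol times these two forms in several places.

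- Section 2, Design/Methodology: "Demographic information, the IPL will be assessed at the time of enrollment".
- Section 4.2.3: "The IPL and the demographics form will be administered via a secure link to REDCap before the first session of the intervention".
- Section 12 table: the consent-and-enrollment row does not list the IPL. Both forms appear in the next row, headed "Randomization and communication on begin of intervention", where after the telephone call the cell reads "Demographics form via REDCap secure link IPL via REDCap secure link".
- Section 12 table, screening/baseline row, which names demographics but not the IPL: "Remotely via REDCap secure link (PHQ9, GAD7, PCL5, LEC5, demographics, exclusion criteria".

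The start of the intervention differs by arm. Section 5 describes it as something "which occurs at randomization for the intervention group, and 12 weeks after for the waitlist control group". Section 2 gives the order for waitlist participants: "Once the endline has been assessed, they will receive the intervention, with corresponding assessments as described previously". Section 12 puts that endline "12 weeks after baseline in waitlist control group".

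Moderation of efficacy by migration experience, integration and demographics is an exploratory objective in Section 4.1 and appears again with the hypotheses in Section 15.1.

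**The concern.** A variable used to ask who benefits more should be measured before allocation and at the same stage in both arms. If it is taken once participants know whether they start now or in 12 weeks, the answers may already reflect that knowledge. If it is taken near randomisation in one arm and after the endpoint in the other, the interaction sets a predictor of later symptoms against a variable measured alongside or after them. Either can create or mask apparent effect modification.

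The IPL covers psychological, economic and social integration, among other domains, and the demographics form asks about employment and residence. These can change over 12 weeks and may move with mood. Section 6.2 itself treats psychological integration as something that can improve. A baseline value that was not collected cannot be recovered later.

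**Working it through.** The protocol gives no figure to reproduce here, so the check compares the timing statements and the gap between arms that each implies.

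**Inputs.** Session 1 falls at randomisation for the intervention arm (week 0) and 12 weeks later for the waitlist (Section 5). The waitlist endline precedes its session 1 (Section 2). Allocation is 60 to 30 (Section 15.2).

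**Gap = waitlist week minus intervention week, by reading.**

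- At enrollment (Section 2): 0 − 0 = 0 weeks.
- In the randomisation step (Section 12): 0 − 0 = 0 weeks.
- Before session 1, link sent early (Section 4.2.3): 0 − 0 = 0 weeks.
- Before session 1, link sent just before it (Section 4.2.3): 12 − 0 = 12 weeks, and after the endline in the waitlist.

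One reading of four separates the arms. If it were followed for every waitlist participant, 30/90 = one third of the sample would have a post-endline value.

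**Is completion before allocation secured?** Section 2 comes closest, because enrollment precedes randomisation in the Section 12 table. But that table leaves the IPL out of its enrollment row and puts it in the randomisation row, without saying whether the forms come before or after the allocation is drawn or announced. Section 4.2.3 does not mention randomisation. For demographics the position is better: the screening row names them, and Section 10 collects age, nationality and date of arrival at screening. Neither place shows that the full form, including employment and residence, is completed then.

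**Illustration only.** The protocol gives no correlations, so these are assumed. Suppose the IPL correlates −0.25 with later symptoms (intervention arm, measured early) and −0.40 with symptoms when measured late (waitlist).

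- SE of the slope difference = √[(1 − 0.25²)/60 + (1 − 0.40²)/30] = √(0.0156 + 0.0280) = 0.209.
- Spurious difference = 0.40 − 0.25 = 0.15, so the shift is 0.15/0.209 = 0.72.
- P(|Z + 0.72| > 1.96) ≈ 0.11, against a nominal 0.05.
- With the same SE, a difference of 0.10 gives about 0.08 and 0.05 gives about 0.06.

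The range of about 6% to 11% applies only if all waitlist participants are measured late and an IPL-by-arm test is run.

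**The case against.** The strongest reply is that the statements can largely be reconciled. Section 4.2.3 sets a latest time, and completion at enrollment or at the randomisation call meets it in both arms. The schedule also points away from late collection: neither the endline row nor the during-intervention row of the Section 12 table includes the IPL, and no slot places it after the waitlist endline. If the forms did follow allocation at the randomisation call, both arms would still complete them at the same step. The analysis is exploratory, in a pilot sized for problem detection, and Section 15.3 names only sex as an effect modifier to be tested. The Appendix schedule of events, which is not in the text available, may settle the timing.

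Most of this stands. A reader might infer that the protocol has controls complete the IPL after their endline, that two of the placements are definitely post-randomisation, or that the moderator analysis does compare different stages by arm. The documents support none of these: late collection is permitted rather than scheduled, and the order within the randomisation row is not given.

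The reply does not remove the remaining gap. Sections 2 and 12 put the IPL at two steps that the table itself separates, and the table's placement does not protect against answers given after allocation is known. Staff who sent waitlist participants the link just before their session 1 would still comply with Section 4.2.3.

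**Conclusion.** The point holds as an inconsistency that leaves a named moderator unprotected, not as a demonstrated bias. The moderator analysis may use values taken after allocation is known, or at different stages by arm.

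The exposure runs from no gap between arms to about 12 weeks for up to one third of participants, depending on how staff read Section 4.2.3. It concerns the IPL and changeable items such as employment and residence; age and arrival date are hardly affected. No primary or secondary outcome depends on it. The false-positive range rests wholly on assumed correlations and on a test that the protocol does not spell out, so it should not be quoted as the size of the problem. The correction is worth making because it costs almost nothing and a missed baseline value cannot be recovered.

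**What to change.** In Section 4.2.3 and the Section 12 table, state that every participant in both arms completes the IPL and the full demographics form after participation consent and before the allocation is drawn. Move both forms from the randomisation row to the consent-and-enrollment row, and replace the first-session deadline in Section 4.2.3. Say which demographic items are taken at screening for eligibility, so that the two collections do not conflict. Check that the Appendix schedule agrees. State that only these pre-allocation values will be used as moderators.

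The cost is protocol wording and the timing of links that are already planned. No instrument, visit or participant is added.

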## 5 Study Design

This is a randomized pilot study with waitlist control with the aim to compare trends in outcomes between the intervention and control group. Following the intent-to-treat principle, all randomized subjects will be included in the analyses. The sample size for pilot participants is based on a simple method outlined by Viechtbauer, which suggests a sample size of  $n = 60$  will be adequate for problem detection. As no treatment exists for forcibly displaced populations, we will randomize  $n = 30$  to waitlist control and treat all participants. The randomization process to intervention or waitlist control will be carried out by a random number generator. Participant with odd numbers will be assigned to the active treatment group and participants with even numbers to the waitlist control group.

The study population comprises outpatient participants, with symptoms of common mental health disorders such as anxiety, depression and/or PTSD (inclusion criteria are described in detail in section 5), adult ( $\geq 18$  years old), male and female, of Venezuelan nationality, that

Adaptation and assessment of a common element treatment protocol designed to improve mental health in forcibly displaced populations  
Version 1, September 17, 2024  
have arrived in Lima in years 2014 to the present.

There will be a planned variation in the dosage of the intervention, which can comprise 6 to 12 sessions. The exact number of sessions will be implemented according to the presentation of symptoms and difficulties of the participant. For instance, if the participant presents depressive symptoms concurrent with PTSD, then, strategies for the treatment of depression will be included alongside with strategies for the treatment of PTSD and the number of sessions will be higher. Also, some components identified as important for this population, such as problem solving or emotional regulation, could be added to the intervention, if they are identified as relevant for the specific participant. For instance, if - alongside with the CMD symptoms - the participant presents concrete problems that need to be tackled (e.g. precarious housing conditions, or lack of and need of childcare support), then the “problem-solving” component will be included as part of the intervention and the number of sessions will be higher. As described in detail in Section 8 “Study Intervention”, the first 6 sessions will be intended to treat the most urgent symptoms, and the following sessions will tackle other aspects relevant to the mental health of the participants.

As to the collection of data for the assessment of study objectives, the participant outcomes will be measured using validated instruments such as the PHQ9, GAD7, LEC5 and PCL5. In the case of the intervention group, all outcomes will be measured in the screening, after the last session and at 1-, 3- and 6-month follow-up. In the case of waitlist control, primary outcomes will be assessed at baseline during screening and at endline 12 weeks after baseline. For both the waitlist control and the intervention group, The PHQ9, GAD7, and PCL5 will be assessed throughout the intervention (which occurs at randomization for the intervention group, and 12 weeks after for the waitlist control group).

Furthermore, the assessment of secondary outcomes, such as acceptability and feasibility, will be measured as presented above, in section 4.

See the Appendix for a schematic of the study design.

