|                                        | will be identified and trained as supervisors. Following the training, these supervisors lead small practice groups and supervision groups, closely supported and supervised by psychologists. We will engage a total of $n = 10$ providers, each of which will engage with $n = 9$ participants ( $n = 6$ pilot, $n = 3$ waitlist control).                                                                                                                                                                                                                                                                                                                                                                                                                                                                                                                                                                                                                                                                                                                                                                                                                                                                                                                                  |

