## 12 Study Procedures

See the Appendix for the schedule of events.

| Phase       | Time                                                                                                         | Description                                                                                                                                                                                                                                                                                                                                                      |
|-------------|--------------------------------------------------------------------------------------------------------------|------------------------------------------------------------------------------------------------------------------------------------------------------------------------------------------------------------------------------------------------------------------------------------------------------------------------------------------------------------------|
| Recruitment | 
Begin: January 2025
 
End: When n = 90 is reached (n = 60 intervention; n = 30 waitlist control)
 | 
Opt-in: Potential participants learn about the study and contact the research team. Information is shared via
 
 
• Posters in the front of organizations NGOs active in migration, health centers and community mental health centers, shelters, schools
 
• Flyers available at these institutions
 
 |

|                                                          |                                                                                                                                                                      |                                                                                                                                                                                                                                                                                                                                                                                                                                                                                                                                                                                                            |

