### 15.2 Sample Size Determination

The sample comprises  $n = 90$  pilot participants, of which  $n = 60$  will be randomly assigned to the intervention group and  $n = 30$  to a waitlist control. The sample size for pilot participants is based on a method outlined by Viechtbauer. Viechtbauer suggests that for a pilot trial a sample size of  $n = 59$  is sufficient to detect a problem that emerges for 5% of participants.

We expect participant recruitment to be feasible as the PI and colleagues at Universidad del Pacifico have recruited and engaged with over 2,000 research participants in mental health research. For example, for the prior stages of this project we have engaged  $n = 19$  experts and  $n = 29$  migrants.

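### The odd/even allocation rule is 1:1 under any ordinary number range and contradicts the planned 60:30 (2:1) split

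*Protocol*

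**What the plan says.** The allocation rule appears once, in Protocol section 5: "The randomization process to intervention or waitlist control will be carried out by a random number generator", followed by "Participant with odd numbers will be assigned to the active treatment group and participants with even numbers to the waitlist control group". The section gives no number range, weighting, blocking or procedure for a full arm.

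The planned split is 2:1 wherever it is given:
- The Population and Design/Methodology rows of section 2 give 60 intervention and 30 waitlist.
- The Intervention row of section 2 gives the load for each of 10 providers: "each of which will engage with $n = 9$ participants ( $n = 6$ pilot, $n = 3$ waitlist control".
- Section 12 ties the end of recruitment to the arm counts: "End: When n = 90 is reached (n = 60 intervention; n = 30 waitlist control".
- Section 15.2 repeats 60 and 30 out of 90.

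Section 5 also sets the analysis principle as intent-to-treat, under which "all randomized subjects will be included in the analyses".

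**The concern.** A 1:1 rule and a 2:1 target cannot both be carried out as written, except by rare chance. Whoever runs the allocation must depart from one of them, and the Protocol does not say which.

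The harm depends on how the conflict is settled. If the rule is kept and the counts are allowed to drift, the trial stays randomised but ends far from its planned numbers and provider workload. If the counts are kept by closing the waitlist once it has 30 people, everyone enrolled afterwards goes to the intervention by default. The research team runs screening and consent (sections 10 and 11), so it would know the next assignment before enrolling the person.

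This matters because efficacy is the primary objective (section 4.1), the hypothesis is a comparison with waitlist (section 15.1), and outcomes are tested at two-sided 0.05 (section 15.3). People assigned by default were not randomised, so they do not fit the intent-to-treat set. The screening script in section 10 also tells candidates that their timing of treatment is decided at random, which would be untrue for them.

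**Working it through.** **Planned figures.** Section 2: 10 providers × 6 = 60 intervention, 10 × 3 = 30 waitlist, total 90. This agrees with sections 12 and 15.2, so the target is consistently 60:30.

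**Probability under the stated rule.** The share of odd integers in 1 to 10, 1 to 90 or 1 to 100 is 1/2, and in 1 to 99 it is 0.505. I take p = 0.5. If the odd and even numbers were instead sequential participant numbers, 90 people would split exactly 45:45.

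**Rule followed for 90 people.** The number in intervention is Binomial(90, 0.5).
- Mean = 90 × 0.5 = 45; SD = √(90 × 0.25) = 4.7
- 95% range: 36 to 54
- P(exactly 60) = C(90,60) × 0.5^90 = 0.00054, about 0.05%
- P(60 or more) = 0.0010, about 0.1%

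**Rule followed until intervention reaches 60.** Expected total = 60/0.5 = 120, with about 60 on the waitlist. Nobody is assigned without randomisation, but the planned 90 is exceeded by about 30.

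**60:30 forced at 90 by closing full arms.** This procedure is inferred; the Protocol does not state it.
- Enrolments until the 30th waitlist place is filled: mean 30/0.5 = 60; SD = √(30 × 0.5)/0.5 = 7.7
- Assigned by default: 90 − 60 = 30 on average, which is 30/90 = 33% of the trial and 30/60 = half of the intervention arm
- In 400,000 simulated trials with caps of 60 and 30, the mean was 30.0 and the central 95% range 13 to 44 (14% to 49% of 90). The waitlist filled first in 99.9% of them.

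**Caps applied more locally.** Section 12 starts sessions in three groups of 30 and section 2 plans 6:3 per provider.
- 20:10 within each group of 30: 10.1 of 30 assigned by default, 34%
- 6:3 within each provider: 3.4 of 9 assigned by default, 38%

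Local caps do not reduce the share assigned by default, but they spread those assignments over the enrolment period.

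**After the fix.** Simple allocation with probability 2/3 centres on 60:30 but still varies: SD = √(90 × 2/9) = 4.5, P(exactly 60) = 8.9%, P(55 to 65) = 78%. A list of complete 2:1 blocks totalling 90 gives exactly 60:30. For example, 10 blocks of 3 and 10 blocks of 6 make 30 + 60 = 90, of which 20 + 40 = 60 are intervention.

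**The case against.** **No cap is stated.** Section 12 gives counts at which recruitment ends, not an instruction for a full arm. This stands. A reader might infer that the Protocol plans to assign a third of participants without randomisation. It does not say so, and the figure is only the average result of one way of forcing 60:30.

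**The uncapped result does little harm to the comparison.** This also stands. A 45:45 split is properly randomised and, with equal variances, slightly more precise: 1/45 + 1/45 = 0.0444 against 1/60 + 1/30 = 0.0500. What remains is a departure from the planned numbers and workload.

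**Concurrent controls are lost only under a single trial-wide cap.** With caps inside each group of 30, every group would have its own waitlist participants and the confounding with calendar time would be much smaller. Predictability of the later assignments would remain.

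**The generator's range might be unusual.** Integers 1 to 3 give odd numbers with probability 2/3. No such range is stated, and it would be an odd way to describe 2:1 allocation, but the accurate wording is that the rule almost never gives 60:30, not that it cannot.

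**Problem detection.** A reader might infer that 45 in the intervention arm undermines the 59 in section 15.2, the number said there to be one that "is sufficient to detect a problem that emerges for 5% of participants". That figure reproduces if 95% confidence is assumed: ln(0.05)/ln(0.95) = 58.4, so 59. But sections 2 and 5 have the waitlist treated after its endline, so about 90 people are due the intervention whatever the split. Before dropout, the chance of seeing a 5% problem at least once is 1 − 0.95^90 = 99.0%. The documents do not support a shortfall here.

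**Alternation.** A reader might take the odd/even sentence to mean allocation by enrolment order. The sentence before it names a random number generator, so I do not claim that.

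**Conclusion.** The contradiction holds and lies wholly within the Protocol: the only stated allocation rule is 1:1, and the planned split is 2:1 everywhere. It rests on one assumption, that the generator's range has as many odd as even numbers or nearly so.

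Followed as written with 90 people, the rule misses the plan by about 15 participants per arm (45 against 60, and 45 against 30). The more serious consequence, about 30 people assigned predictably and outside randomisation, is conditional on staff closing the waitlist at 30. The section 12 recruitment condition makes that plausible but does not prescribe it. Under one trial-wide cap those people would also be the last enrolled and would lack concurrent controls.

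This is not a detail that a statistical analysis plan could settle, because assignments already made cannot be corrected in the analysis. It should be settled before the first participant is allocated.

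**What to change.** Replace the odd/even sentence in section 5 with a 2:1 permuted-block list that is:
- generated in advance in complete blocks totalling 90, with mixed sizes, for example 3 and 6
- kept, with its block sizes, from the staff who recruit and consent; in an open trial, a waitlist draw at the start of a known block of 3 reveals the next two assignments, and mixing sizes reduces this without removing it
- held in REDCap, with each assignment revealed only after consent and baseline assessment are complete.

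Add one sentence stating that no participant is assigned because an arm is full.

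Alternatively, keep 1:1 and restate the plan as 45:45 in sections 2, 5, 12 and 15.2, including the 6 and 3 per provider. That is equally sound for the comparison, but it puts 15 more people on the waitlist than planned (45 − 30).

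The first option costs one paragraph and a list loaded into a system already in use; the second costs edits to the counts. Neither needs extra participants or visits.
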